### Recruitment

2.5

It will be a study enrolling patients with NSLBP meeting inclusion and exclusion criteria at the designated hospital. Recruitment will be conducted by the medical staff at the hospital, which will identify such patients upon their intake and extend an invitation. Then, an initial face-to-face interaction with patients by the study team will take place, in which patients will be briefed on objectives, methods of the study, possible benefits, and potential risks. Invited patients will be brought to the hospital for a thorough health evaluation, involving a comprehensive history of their pain, as well as symptoms. Once study details have been clearly explained to the participant and their questions answered, they will be asked to sign an informed consent. Only after signing the document will patients be officially enrolled in the study.

### Informed consent

2.6

The informed consent process will be carried out transparently and openly, with strict adherence to ethical principles. NSLBP patients meeting inclusion and exclusion criteria will be presented with a thorough written explanation of study aims, procedures, possible risks and rewards, and measures to protect patients’ privacy, including meticulous details of collecting, storing, and protecting their information. We will take care to keep all data securely on encrypted computers that only approved study members can access, only for the duration of the study, and will be properly destroyed upon study completion. Individuals will have ample time to read carefully through the consent form, ask questions, and provide consent voluntarily. Participants will be made aware clearly that they can withdraw from study participation at any time without adverse effects. Ongoing consulting contact information will be made available by the study team so that people can seek additional information or explanation at any time. Participants will receive any new information during the study that could influence participation continuation so that ongoing consent is maintained.

In addition, no penalties will be levied upon participants who choose to withdraw from the intervention arm. Patients who withdraw if intervention has already started cannot be reassigned to the control arm and will be counted as natural attrition cases. Where possible, semi-structured interviews with withdrawing participants will be undertaken to examine reasons for departure. Participants will be explicitly made aware of all accessible modes of follow-up in the event of withdrawal through an informed consent process, so that they understand all their rights and options well.

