#### Withdrawal criteria

2.3.3

Participants who voluntarily request to withdraw from the study for personal reasons, such as scheduling conflicts or changes in interest;Occurrence of severe adverse events during the study, such as serious physical illnesses or acute events (e.g., heart attack, severe infection) that require interruption of the intervention;Changes in medical condition or other medical advice that necessitate altering the original treatment plan, potentially conflicting with the study intervention.

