#### Control group

2.7.1

Control group members will be assigned to receive standard medical care by a multidisciplinary medical team. Healthcare services will consist of: (1) routine consultations with doctors for health check-ups and treatment regimen modifications; (2) follow-up visits after predetermined intervals to track disease progression; (3) thorough diagnostic evaluations to follow health indicators; (4) formal educational sessions addressing management of the condition, treatment compliance, and change of lifestyle; and (5) referrals to specialized medical care providers if clinically warranted. This approach maintains consistency with clinical practice guidelines and standard protocols for routine management of asthma.

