
### Statistical analysis

2.13

In this study, quantitative data will be collected through questionnaires and stored in Microsoft Excel format. Data analysis will follow the intention-to-treat principle. For continuous variables, results will be presented as mean ± standard deviation or as median with interquartile range (P25, P75), depending on the normality of the distribution, which will be assessed using the Kolmogorov–Smirnov test. Appropriate statistical methods, such as Student’s t-test, one-way ANOVA, or non-parametric tests, will be used for group comparisons. Categorical variables will be expressed as counts and percentages (n, %) and analyzed using the chi-square test.

To explore the relationships between behavioral patterns and mobile health application use, linear regression, logistic regression, and structural equation modeling will be applied to cross-sectional data. For longitudinal analyses, generalized linear mixed models will be used to assess the impact of AI-HEALS interventions on behavior change and NSLBP management over time. Subgroup analyses will be conducted based on patients’ levels of family communication and eHealth literacy to refine and contextualize the findings.

Missing data will be addressed using multiple imputation by chained equations (MICE), with 50 iterations to ensure convergence. Predictive mean matching (PMM) with five nearest neighbors will be employed, generating 20 imputed datasets. All statistical tests will be two-sided, with a significance level set at 0.05. Data will be analyzed using IBM SPSS Statistics 24.0 (SPSS Inc., Chicago, IL, United States), Stata 14.0 (StataCorp, College Station, TX, United States), and Mplus 7.4 (Muthén & Muthén, Los Angeles, CA, United States).

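### Stopping AI-HEALS is not separated from leaving the study, and no later VAS is promised for patients who stop, which undermines the intention-to-treat analysis

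*Protocol article*

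**What the plan says.** All references are to the protocol article.

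- **Section 2.6 (Informed consent)** first says that "no penalties will be levied upon participants who choose to withdraw from the intervention arm". The next sentence reads: "Patients who withdraw if intervention has already started cannot be reassigned to the control arm and will be counted as natural attrition cases". The same paragraph adds: "Participants will be explicitly made aware of all accessible modes of follow-up in the event of withdrawal".
- **Section 2.3.3 (Withdrawal criteria)** gives three grounds. One is voluntary: "Participants who voluntarily request to withdraw from the study for personal reasons, such as scheduling conflicts or changes in interest". One is a severe adverse event or acute illness of a kind "that require interruption of the intervention". The third is: "Changes in medical condition or other medical advice that necessitate altering the original treatment plan, potentially conflicting with the study intervention".
- **Section 2.13 (Statistical analysis)** states: "Data analysis will follow the intention-to-treat principle". Missing data are to be handled by chained-equations multiple imputation with predictive mean matching and 20 imputed datasets.
- **Section 2.10.1 and Table 1** schedule VAS, the primary outcome, at baseline, discharge, the end of the 3-month intervention, and 3, 6 and 9 months after it.
- **Section 2.10.2** collects dropout rates and reasons, and plans to compare dropouts' characteristics and outcomes.
- **Section 2.4** allows for 20% attrition overall.

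**The concern.** Intention-to-treat needs outcomes from every randomised patient, including those who stop the assigned treatment. Here one word, withdrawal, covers two different events: giving up AI-HEALS and leaving follow-up. Section 2.6 speaks of withdrawing from an arm and then classes those patients as attrition. Section 2.3.3 speaks of withdrawing from the study, but gives grounds that concern interruption of, or conflict with, the intervention. Site staff who follow this wording could reasonably stop collecting VAS once a patient stops the intervention.

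Calling the loss natural suggests that it carries no information. A change in condition or in the treatment plan may well be related to pain. Because two criteria are tied to the intervention, they may also be applied more often in the arm that has one. Loss that is related to outcome and unequal between arms biases the treatment comparison, and the planned imputation removes that bias only as far as the observed data explain why patients left.

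**Working it through.** **1. The plan's own figure.** Section 2.4 gives 29 per group, raised to 37 for 20% attrition: 29 / 0.80 = 36.25, rounded up to 37, so 74 in total. This reproduces. With d = 0.68, one-sided alpha 0.05 and power 0.80, a t-test needs 28 per group and a Wilcoxon-Mann-Whitney test 29, so the stated 58 is also in line. The 20% is all-cause and covers both arms. It says nothing about how losses divide by arm or reason.

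**2. What a withdrawn patient loses.** VAS is scheduled six times. A patient withdrawn after discharge but before the end of the intervention keeps two assessments (baseline and discharge) and loses four of the five post-baseline ones. The imputation then rests on two VAS values that usually precede the event that led to withdrawal. Missing at random is hardest to defend in that situation.

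**3. Size of bias under stated assumptions.** The article has no withdrawal rates by arm or reason, so the following inputs are assumptions:
- w: share of the intervention arm lost, 10% or 20%, with no loss in control.
- k: how much worse the unseen outcomes are than predicted from observed data, in SD units, 0.25 to 1.0.

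If the analysis assigns the lost patients a mean m but their true mean is worse by k, the true arm mean is (1 − w)·m + w·(m + k) = m + w·k. The arm therefore looks better than it is by w·k.

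| w | k | bias w·k (SD) | share of 0.68 | two-sided rejection rate if there is no true effect |
|---|---|---|---|---|
| 10% | 0.25 | 0.025 | 4% | 5.1% |
| 10% | 0.5 | 0.05 | 7% | 5.5% |
| 10% | 1.0 | 0.10 | 15% | 7.0% |
| 20% | 0.25 | 0.05 | 7% | 5.5% |
| 20% | 0.5 | 0.10 | 15% | 6.9% |
| 20% | 1.0 | 0.20 | 29% | 12.6% |

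The rejection rates use a noncentral t with 37 control patients and 33 (w = 10%) or 30 (w = 20%) intervention patients.

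**4. When the bias shrinks or reverses.** With loss in both arms the bias is w_I·k_I − w_C·k_C (I = intervention, C = control). At 20% and k = 0.5 in each arm it is 0.10 − 0.10 = 0. If intervention patients leave because they feel better, k is negative: w = 20% and k = −0.5 gives −0.10 SD, against AI-HEALS. If VAS is still collected after stopping, w for this reason is zero and so is the bias.

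**The case against.** The strongest reply is that nothing here conflicts with intention-to-treat. Barring a move to the control arm is what that principle requires. Classing someone as attrition does not remove them from the analysis, and section 2.13 imputes missing values. This stands. A reader might infer that the plan contradicts intention-to-treat, but no section excludes withdrawn patients from analysis.

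A reader might also infer that poor responders are removed mainly from the intervention arm. The article does not support that:
- No criterion mentions pain or lack of response. The examples are acute illness, scheduling conflicts and loss of interest.
- Voluntary withdrawal applies to either arm.
- It is tempting to contrast the control arm, where section 2.7.1 lists "routine consultations with doctors for health check-ups and treatment regimen modifications" as ordinary care. According to the abstract, however, the intervention arm receives standard care as well, so this contrast does not show unequal removal.

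Section 2.6 does mention follow-up after withdrawal, so it is not settled that patients leave altogether. But this is an option explained at consent, not a commitment to scheduled VAS. Likewise, the dropout comparison in section 2.10.2 does not say that outcomes are collected after withdrawal.

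The attrition sentence follows one about patients who choose to withdraw, so applying it to the condition-related criteria is an inference. That is fair. Even so, neither section provides for later VAS under any of the three grounds.

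Finally, a journal article leaves detail to the full protocol or the analysis plan. The point here rests on the rules that the article does state, and an analysis plan cannot restore data that were never collected.

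**Conclusion.** The point holds as a weakness in the withdrawal rules. Sections 2.3.3 and 2.6 merge stopping the intervention with leaving the study, tie two criteria to the post-randomisation course and to the intervention, and make no commitment to later VAS. This undermines the stated intention-to-treat analysis, because the loss may depend on outcome and may differ between arms.

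The size is unknown. The range of 0.025-0.20 SD (4-29% of the planned 0.68) rests on three assumptions that the article does not supply: loss confined to the intervention arm, a loss of 10-20%, and unseen outcomes 0.25-1.0 SD worse after conditioning on observed data. Equal loss in both arms would cancel the bias, and departure after improvement would reverse it. This is a worthwhile, inexpensive improvement rather than a fatal flaw. It should be made while follow-up is still running, since the trial is expected to end in December 2026.

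**What to change.** Amend sections 2.3.3 and 2.6 as follows:

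1. Define two separate events: the patient stops the intervention, or the patient withdraws consent to follow-up.
2. In both arms, keep patients who stop the intervention or meet a condition-related criterion on every scheduled VAS and questionnaire assessment, by telephone or WeChat where a visit is not possible, and analyse them in their randomised arm.
3. Count only withdrawal of consent, death or loss of contact as attrition, and drop the description of it as natural.

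The clinical grounds for stopping stay as written.

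The cost is an amendment, revised consent wording and some extra remote questionnaires for patients whom the trial already tracks (section 3). The effect estimate may be slightly diluted, because it will include patients who stopped AI-HEALS.

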### Intervention

2.7

#### Control group

2.7.1

Control group members will be assigned to receive standard medical care by a multidisciplinary medical team. Healthcare services will consist of: (1) routine consultations with doctors for health check-ups and treatment regimen modifications; (2) follow-up visits after predetermined intervals to track disease progression; (3) thorough diagnostic evaluations to follow health indicators; (4) formal educational sessions addressing management of the condition, treatment compliance, and change of lifestyle; and (5) referrals to specialized medical care providers if clinically warranted. This approach maintains consistency with clinical practice guidelines and standard protocols for routine management of asthma.

#### Intervention group

2.7.2

Based on earlier RCTs conducted on NSLBP (33), this trial uses a 3-month intervention duration. Throughout these 3 months, AI-HEALS will administer intervention to the intervention arm through the “NSLBP Health Management Expert” WeChat system. Intervention members include public health professionals, clinicians, clinical nurses, psychologists, and statisticians. Intervention program components consist of four major components:

·NSLBP Knowledge-Based Question-Answering System (KBQA): This system will enable NSLBP patients to better understand their illness. It works with a frequently asked questions robot (FAQrobot), which allows participants to access NSLBP knowledge efficiently and accurately. To make this possible, we will compile a robust and accurate NSLBP knowledge base encompassing various aspects such as general knowledge of the disease, causes, symptoms, treatment procedures, use of medications, day-to-day management, appropriate diet, and relevant physical exercise. We will incorporate this knowledge base into ByteDance’s large language model (LLM), which will enable the model to learn from the database and respond to questions professionally on the WeChat site. In addition, to make user interaction and engagement stronger, three relevant questions will be presented each time a user submits an inquiry, promoting in-depth exploration and interaction. To adaptively improve the knowledge base and respond to users’ demands, we will record participants’ query behaviors (e.g., system access times, frequencies) and uses in the system backend. By exploring these data, we can understand behavioral patterns based on which we improve and advance the knowledge base and question-answering system in such a way that information timeliness and accuracy are ensured. During the process of Q&A interaction, the system offers both text and voice inputs, which notably reduces the threshold for operation and allows broader accessibility (Figure 2).·Recording Lifestyle Factors and Physiological Indices: AI-HEALS will assist NSLBP patients in documenting regularly their factors of lifestyle, namely week-by-week medications, foods consumed, exercise, etc. Participants can enter information in real-time, and it is possible for researchers to view recorded information through the backend interface. This will allow long-term tracking and monitoring of self-management practices. In order to make the data relevant and accurate, the team conducting the study will engage with the patients’ families at an early point in participation to design SMART (Specific, Measurable, Achievable, Relevant, Time-bound) plans. Data collection will be centered on these plans, with system-generated reminders being sent to all study participants annually on every Saturday to encourage them to upload rich information. This will enable a thorough examination of the intervention’s effects on patients’ everyday living in addition to ensuring that data captures the individual goals of each participant (Figure 3B).Personalized Reminder Service: To improve treatment adherence, the AI-HEALS system will offer personalized reminder services. Participants may easily configure reminders for different significant activities like drug intake and physical exercise. Once such reminders are configured, the system will provide reminders based on these specified times. This reminder feature will assist patients in strictly following medical advice, enhance long-term adherence to healthy behaviors, and ultimately aid them in managing their NSLBP (Figure 3A).·Automated & Personalized NSLBP Education Articles for Patients: The system will also run an automated system for dispensing education articles. One to three education articles on topics related to managing pain will be sent every week to NSLBP patients. Examples of topics include exercise advice that helps patients with types of exercise that are appropriate and intensities of exercise, along with correct drug information like administration methods and possible side effects to watch for. Education articles will be exactly personalized and distributed depending on participant interaction patterns with the system like types of questions posed, frequency of visits, and areas of interest to address each NSLBP patient’s individual needs. In order to make information dissemination most effective, background data will be regularly checked by the research team, such as assessing read numbers, types of preferred papers, and time spent on each. Following these data, article content and frequency of distribution will be adjusted.

**Figure 2 fig2:**
[figure not shown]
Artificial intelligence health education precision linkage system responses to non-specific lower back pain knowledge.

**Figure 3 fig3:**
[figure not shown]
Reminder and Record Features of Artificial Intelligence Health Education Precision Linkage System. **(A)** Personalized reminder service to improve adherence to treatment and healthy behaviors; **(B)** Recording of lifestyle factors and physiological indices to facilitate long-term monitoring and self-management.

### Overview of the artificial intelligence system

2.8

“Doubao-pro-32 k,” a Chinese-trained Transformer model optimized for medical knowledge application, was deployed in this study. Doubao-pro-32 k was trained by merging biomedical literature with pain-related clinical guidelines, after which it was fine-tuned on a 32 k context window to produce long-text health education content. Pre-training in general language understanding was carried out on the model before domain-specific fine-tuning to improve medical reasoning ability. Third-party performance benchmarking on the FlagEval evaluation platform^1^ revealed that “Doubao-pro-32 k” scored competitively with GPT-4o. Indeed, overall, “Doubao-pro-32 k” scored 77.75 points, beating GPT-4o’s 73.51 points. Its greatest strength lies in knowledge application (Doubao-pro-32 k: 91.14, GPT-4o: 86.71), an ability that is essential in producing evidence-based clinical information. On development, domain experts performed an initial review of the output from the model to confirm consistency with current medical knowledge and compliance with high levels of medical evidence-based research. Post-pilot study, a sustained validation program will be implemented, such that two experts review 10% of outputs month to month on a back-to-back basis and estimate rates of accuracy to keep system accuracy sustained.

Finally, under this study, maintaining participants’ privacy and securing data integrity in their interaction with the AI-HEALS system are top priority. Any patient data collected through the AI-HEALS system will be held with utmost confidentiality and only for purposes of conducting this study. Each member of our study team is bound by applicable privacy and confidentiality agreements, so both legally and ethically, they are bound to secure participants’ sensitive information. In addition, study participants are entitled to withdraw from participation unconditionally at any point in time without any grounds. This respect for participants’ autonomy guarantees that study members are not pushed to continue. Lastly, all adverse events resulting from intervention will be carefully documented and reported in accordance with local regulations and stipulated procedures.

### Strategies to improve adherence to interventions

2.9

In order to ensure participant compliance, we will: (1) clearly discuss participant responsibilities upon participation in the observational period at study recruitment and upon signing of the informed consent. Simultaneously, we will work diligently to establish sound participant relationships to enable mutual trust. (2) Offer thorough education and counseling regarding disease management and prevention strategies throughout study. We will discuss disease characteristics, stress the need for strict treatment compliance, and provide tips for avoiding potential complications. (3) Weekly review by the research team of intervention group interaction with the system will ensure maximum participant engagement. Ongoing review will warrant early detection of any problem or disengagement, so that corrective actions can be initiated by the research team and participant engagement maintained.

### Outcomes

2.10

#### Primary outcomes

2.10.1

Changes in pain intensity from baseline to discharge, at the end of the intervention, and during follow-up periods at 3, 6, and 9 months post-intervention.

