In this context, the deployment of the Artificial Intelligence-Health Education Accurately Linking System (AI-HEALS) via WeChat, China’s largest social media site, assumes special relevance. It employs cheap, ubiquitous mobile communication technology so that patients are able to receive support and management from their own homes. AI-HEALS intervention content relies on the HAPA-MTM theoretical model, addressing not only physiological symptom management but also highlighting psychological health and changes in behavior, providing an integrated and extended approach to disease management (35–37). Highlight of the system includes AI-based knowledge Q&A from a tailored knowledge base, tracking of physiological markers and behaviors, different reminder services, and message dissemination tailored to each individual. Such an innovative intervention model is well-suited for contemporary society’s needs and can potentially provide efficient support and management for many patients with NSLBP.

In summary, this study is intended to assess the efficacy of AI-HEALS intervention program among patients with NSLBP on their self-management outcome by conducting a randomized controlled trial (RCT) in the following areas:

Evaluate the efficacy of the three-month multifaceted AI-HEALS intervention in enhancing physiological indicators among the NSLBP population;Assess the efficacy of the three-month integrated AI-HEALS intervention for improving psychological indicators in the NSLBP population;Evaluate the efficacy of the three-month overall AI-HEALS intervention in enhancing behaviors of self-management among NSLBP individuals.

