### Sample size

2.4

G-Power 3.1.9.4 was used to calculate the sample size. The effect size was 0.68 (33), efficacy was 0.80, alpha was set at 0.05, and one-tailed tests were performed based on previous studies. The calculated required sample size was determined to be at least 58 (29 participants per group). We estimated an attrition rate of 20%, so a total sample of at least 74 participants (37 per group) was required.

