### Variables measurement

2.11

Sociodemographic variables will be collected at baseline. Physical examinations and questionnaire surveys will be conducted at baseline, at discharge, at the end of the intervention, and at 3, 6, and 9 months post-intervention (Table 1).

**Table 1 tab1:** The schedule of enrolment, interventions, and assessments.

Study period	Recruitment	Intervention		Follow-up		
Timepoint	0	Discharge	3 Months	3 Months	6 Months	9 Months
Eligibility screen	√					
Informed consent	√					
Allocation	√					
Sociodemographic variables	√					
VAS	√	√	√	√	√	√
RMDQ	√	√	√	√	√	√
OPFEAS	√	√	√	√	√	√
PHQ4	√	√	√	√	√	√
PSSS-SF	√	√	√	√	√	√
NGSES-SF	√	√	√	√	√	√
EQ-5D-5L	√		√	√	√	√
IPAQ-SF	√		√	√	√	√
Smoking	√		√	√	√	√
Alcohol consumption	√		√	√	√	√
B-PSQI	√		√	√	√	√
SREBQ	√		√	√	√	√
FCS-SF	√					
eHEALS	√					

VAS, visual analog scale; RMDQ, The Roland-Morris Disability Questionnaire; OPFEAS, The Orthopedic Patient Functional Exercise Adherence Scale; PHQ-4, the abbreviated Patient Health Questionnaire-4; PSSS-SF, The Perceived Social Support Scale; NGSES-SF, The New General Self-Efficacy Scale-Short Form; EQ-5D-5L, EuroQol-5 Dimensions 5 Levels; IPAQ-SF, The International Physical Activity Questionnaire Short Form; B-PSQI, The new Brief Version of the Pittsburgh Sleep Quality Index-Short Form; FCS-SF, The Family Communication Scale-Short Form; SREBQ, The Self-Regulation of Eating Behavior Questionnaire; eHEALS, The eHealth Literacy Scale.

Sociodemographic variables to be collected include gender, age, marital status, location, average household size, educational level, and occupation, along with clinical information such as the duration of NSLBP and detailed medical history. Anthropometric variables: Each participant’s height, weight, waist circumference, and blood pressure will be measured twice using certified instruments. Height and weight will be measured using fully calibrated, certified electronic devices. Body Mass Index will be calculated by dividing weight (in kilograms) by height (in meters) squared. Waist circumference will be measured at the level of the navel using a tape measure. As for blood pressure, systolic and diastolic pressures will be measured using a validated automatic sphygmomanometer.

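### The primary outcome is pain change at five post-baseline visits with no primary visit or success rule fixed, so a primary claim could rest on any one of five tests at 0.05

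*Protocol article*

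**What the plan says.** Section 2.10.1, headed as the primary outcomes, lists "Changes in pain intensity from baseline to discharge, at the end of the intervention, and during follow-up periods at 3, 6, and 9 months" post-intervention. Section 2.11 and Table 1 confirm that the VAS is taken "at baseline, at discharge, at the end of the intervention, and at 3, 6, and 9 months post-intervention", which is one baseline and five later assessments. No section singles out one of the five.

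Section 2.13 names two kinds of analysis that could carry the primary comparison. Student's t-test, one-way ANOVA or non-parametric tests "will be used for group comparisons". For longitudinal analyses, "generalized linear mixed models will be used to assess the impact of AI-HEALS interventions on behavior change and NSLBP management over time". It then adds: "All statistical tests will be two-sided, with a significance level set at 0.05". No order of testing, adjustment or rule for declaring success is given.

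Section 2.4 rests on one comparison: "The effect size was 0.68 (33), efficacy was 0.80, alpha was set at 0.05, and one-tailed tests were performed". It continues: "The calculated required sample size was determined to be at least 58 (29 participants per group"), raised to 74 (37 per group) for 20% attrition. The visit to which the effect size applies is not stated.

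**The concern.** A primary outcome is complete only when it has a time point, or a stated way of combining time points. Here the variable is fixed and the time is not. As written, the sponsor could report a positive primary result on the strength of whichever visit crosses 0.05, by t-test or by a model contrast. If pain differed at discharge but not at three months, or at nine months only, the plan offers no agreed reading of the result.

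The choice of visits raises a second, separate matter. Four of the five are tied to the end of a programme of stated length. Discharge is not tied to any elapsed time, and Table 1 places it before the 3-month assessment, so a comparison there tests only part of the intervention.

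A detailed adjustment method can be left to an analysis plan. The primary time point is different: it defines the endpoint and anchors the sample size. The protocol is also not silent, since it fixes five points and one blanket significance level.

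**Working it through.** **1. The plan's own figure.** Inputs from Section 2.4: d = 0.68, power 0.80, alpha 0.05 one-tailed, two equal groups.
- Normal approximation: n per arm = 2(1.645 + 0.842)² / 0.68² = 12.37 / 0.4624 = 26.7, so 27.
- Noncentral t: 28 per arm (power 0.807).
- Wilcoxon-Mann-Whitney with relative efficiency 0.955: 29 per arm (power 0.803).
- Attrition: 29 / 0.80 = 36.25, so 37 per arm and 74 in total.

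The stated 29 and 37 are reproduced, to within one patient per arm for the t-test. They are the size for **one** comparison.

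**2. Error rate if any one of five tests counts.** Inputs: five post-baseline visits (Section 2.10.1) and two-sided 0.05 each (Section 2.13). The documents give no between-visit correlation, so it is an assumption and is varied.

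With independent tests, 1 − 0.95⁵ = 0.226. Counting only findings in favour of the intervention, 1 − 0.975⁵ = 0.119. For equally correlated test statistics, P(max|Z| > 1.96) and P(max Z > 1.96) were simulated:

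| Assumed correlation | Any of five, either direction | Any of five, favouring the intervention |
|---|---|---|
| 0 | 22.6% | 11.9% |
| 0.3 | 20.9% | 10.5% |
| 0.5 | 18.3% | 9.2% |
| 0.7 | 14.9% | 7.4% |
| 0.9 | 10.1% | 5.1% |

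For comparison, a single two-sided 0.05 test gives 5% and 2.5%.

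**3. Which row is plausible.** Changes from a shared baseline, with equal variances and equal raw correlations ρ, have covariance proportional to 1 − ρ and variance proportional to 2(1 − ρ). Their correlation is therefore 0.5 whatever ρ is, which gives about 18%. If raw correlations instead decay with time (first-order autoregressive, 0.5 to 0.9), the rate is 16.8% to 14.7%. Simulated t-tests at correlation 0.5 give 18.0% with 29 per arm and 18.4% with 37 per arm, so small-sample effects do not matter.

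**4. Other readings of the same text.** One global mixed-model test over all visits keeps the rate at 5%. One named visit gives 5%. Requiring all five to be significant gives no more than 5%. The plan selects none of these.

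**5. Cost of keeping all five with an adjustment.** Bonferroni at 0.05 / 5 = 0.01 two-sided, d = 0.68: power about 47% with 29 per arm and 61% with 37 per arm. Reaching 80% would need 53 per arm, or 53 / 0.80 = 66.25, so 67 per arm (134 in total). Not all of this loss comes from the adjustment. Unadjusted two-sided power is already about 72% with 29 per arm and 82% with 37 per arm, because Section 2.4 is one-tailed and Section 2.13 two-sided. That mismatch is a separate point.

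**6. Discharge.** Section 2.11 and Table 1 give it no time from randomisation and place it ahead of the 3-month assessment. Section 2.2 houses the two arms in separate wards and says that therapists cannot be blinded. The timing of discharge may therefore differ by arm. This bears on comparability and does not enter the figures in step 2.

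**The case against.** The strongest reply is that the protocol has one primary outcome. The Abstract and the Discussion both speak of pain intensity in the singular, and Section 2.13 assigns longitudinal analyses to mixed models. On that reading the five visits are the repeated measurements of one outcome, and a single global test would hold the error at 5%. This reading is possible, and it is why no inflated rate can be stated as fact. It does not remove the problem. The mixed-model sentence names behaviour change and NSLBP management rather than pain, fixes no contrast or global test, and stands beside separate group-comparison tests. A global test would also not say when any benefit occurs.

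Three stronger readings are tempting and go beyond the documents.
- A reader might infer that the primary false-positive rate is 15% to 20%. That needs an any-of-five success rule, which is nowhere stated, and a correlation of roughly 0.4 to 0.7, which is nowhere given.
- A reader might infer that ward staff set the discharge date, so that the arms are compared at different elapsed times. No section says who decides discharge or that its timing differs. The text shows only that the time is not fixed and that the arms lie in separate wards.
- A reader might infer from the study aims that end of intervention is already the intended primary visit. The first aim begins "Evaluate the efficacy of the three-month multifaceted AI-HEALS intervention" but goes on to physiological indicators, which Section 2.10.2 lists among secondary outcomes. Three months there describes the length of the programme, not an assessment time.

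**Conclusion.** The point stands as a gap in the definition of the primary endpoint: five visits, none named as primary, a blanket two-sided 0.05, no success rule, and a sample size for one unspecified comparison. Its possible size is a primary false-positive rate of about 10% to 23%, of which about 5% to 12% favours the intervention. This is conditional on any one of five separate tests counting as success and on an assumed correlation between 0.9 and 0; at 0.5 the figures are 18% and 9%. Throughout that range the rate is at least twice nominal. Under a single global test it would be 5%, and the fault would then be only that the plan does not say so.

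That discharge is a poor primary time point is a separate conclusion. It rests on the absence of a fixed time and on its place before the end of the programme. A difference in timing between arms is a possibility, not a finding.

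The primary endpoint decides the trial's conclusion, so this must be settled before analysis.

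**What to change.** In Section 2.10.1, name one primary endpoint: VAS change from baseline at the end of the 3-month intervention. In Section 2.13, define it as one between-arm contrast from the mixed model, tested two-sided at 0.05. Make the contrasts at discharge and at 3, 6 and 9 months post-intervention secondary, reported with confidence intervals from the same model. In Section 2.4, state that the calculation refers to the primary contrast. End of intervention is recommended because it is the first assessment after the full programme; the protocol does not itself single it out.

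No new data are needed, since Table 1 already schedules the VAS at every visit. The change is nevertheless a formal amendment. Section 3 requires the Steering Committee, then the Ethics Committee and the research department, and the registry entry must be updated. The trial started in April 2025 and is expected to end in December 2026, so the change should be made, and dated, before anyone sees outcome data by arm. The price is that no primary claim can then rest on any other visit.
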